## Abstract

**Background:**

Licensed premises offer a valuable point of intervention to reduce alcohol-related harm.

**Objective:**

To describe the research design for an exploratory trial examining the feasibility and acceptability of a premises-level intervention designed to reduce severe intoxication and related disorder. The study also aims to assess the feasibility of a potential future large scale effectiveness trial and provide information on key trial design parameters including inclusion criteria, premises recruitment methods, strategies to implement the intervention and trial design, outcome measures, data collection methods and intra-cluster correlations.

**Design:**

A randomised controlled trial in licensed premises that had experienced at least one assault in the year preceding the intervention, documented in police or hospital Emergency Department (ED) records. Premises were recruited from four study areas by piloting four recruitment strategies of varying intensity. Thirty two licensed premises were grouped into matched pairs to reduce potential bias and randomly allocated to the control or intervention condition. The study included a nested process evaluation to provide information on intervention acceptability and implementation. Outcome measures included police-recorded violent incidents, assault-related attendances at each premises' local ED and patron Breath Alcohol Concentration assessed on exiting and entering study premises.

**Results:**

The most successful recruitment method involved local police licensing officers and yielded a 100% success rate. Police-records of violence provided the most appropriate source of data about disorder at the premises level.

**Conclusion:**

The methodology of an exploratory trial is presented and despite challenges presented by the study environment it is argued an exploratory trial is warranted. Initial investigations in recruitment methods suggest that study premises should be recruited with the assistance of police officers. Police data were of sufficient quality to identify disorder and street surveys are a feasible method for measuring intoxication at the individual level.

**Trial registration:**

UKCRN 7090; ISRCTN: 80875696

## Background

Exposure to the night time economy (NTE) environment is associated with an increased likelihood of violent victimisation [1]. Approximately 47% of assaults against adults in England and Wales are committed by offenders believed to be under the influence of alcohol, with a large proportion of incidents taking place at weekends in urban centres [2]. Managing public alcohol use and preventing alcohol-related harm are priorities in numerous jurisdictions across the world and have motivated both policy-level (e.g. the UK 2003 Licensing Act) and individual-level interventions [3]. Accordingly, NTE licensed premises are increasingly the subject of violence prevention initiatives [4]. Legislation on alcohol-related harm and disorder typically focuses on situational preventive measures, such as opening hours regulation, staff training, enforcing the refusal of service to intoxicated patrons, and the replacement of drinking glasses and bottles with plastic alternatives. Such approaches have gained considerable traction across practitioner groups including police, local authority licensing staff and health professionals. In light of the considerable costs due to alcohol-related disorder it is essential that preventive methods are supported by robust evidence. However, few formal evaluations of premises-level interventions have been conducted, and none in the UK [4,5]. Furthermore, it is unclear whether intervention delivery should be targeted at those premises generating the greatest levels of harm or all premises in a NTE. If interventions are to be targeted at problematic premises, it is not clear how these premises should be identified and how they should be recruited into evaluation studies.

Premises-specific risk factors for disorder can be easily identified and therefore managed. Recent legislation that has made premises managers accountable for managing risk in their premises (UK 2003 Licensing Act) has meant that harm and disorder programmes have typically focused on the premises environment rather than the more general NTE environment. The reasoning for this is that the identification and manipulation of situational risk factors can influence the likelihood of an undesirable outcome - a risk factor prevention paradigm. Although a number of studies have identified those characteristics of licensed premises that are associated with harm and disorder [6-8], optimal methods for targeting, recruiting and intervening have not been adequately described in the UK.

Previous evaluations have considered interventions such as responsible beverage server (RBS) training, licensee accords and staff violence reduction training. RBS training, the most commonly evaluated intervention type, typically deploys "off-the-shelf" training packages that do not involve any consideration of premises' underlying risk factors. These unfocused interventions are likely to be less effective than interventions that are responsive to the risks and needs of individual premises. Of the available RCT evaluations that have been conducted in this area, only Graham et al. [9] implemented an intervention that was responsive to the idiosyncratic needs of premises, while Toomey et al. [10] evaluated a not dissimilar risk-led intervention using quasi-experimental methods. Both of these studies concluded that premises-level interventions that are designed to offset risk factors in each premises are feasible.

A range of outcome measures have been used in premises-level evaluations, including police records, rates of hospital treatment following violent injury and customer breath alcohol concentration as well as subjective ratings such as customer self-report and observations of disorder and intoxication by research staff. While convenient, subjective ratings can be susceptible to response and reporting biases. Police records follow a standardised recording protocol, especially after the implementation of a national crime recording standard in England and Wales, that makes them more reliable and appropriate for studying changes in crime over time. As these data also contain information on the location of incidents they can be linked to individual premises. However, police data are susceptible to systematic bias as usually only those incidents that are reported to the police or occur when the police are present are recorded. Emergency Department (ED) data are not susceptible to such biases as serious injury will require hospital treatment irrespective of where and when the assault took place. However, this does mean that ED data are biased towards more serious assaults. ED data are usually collected by reception staff who record details of violence location, time, day and weapon. If the patient declares that their injury is assault-related then this prompts a series of questions about the nature of the incident [11]. In respect of premises proclivity to sell alcohol inappropriately, customer intoxication can be assessed using subjective measures but are inferior to objectively recorded Breath Alcohol Concentration (BrAC) collected using alcometers [12-14].

Of the existing evaluations of premises-level interventions, only three have used a RCT design to measure intervention effectiveness in terms of objectively measured outcomes of intoxication [15,16] or disorder [9]. Furthermore, when matching procedures were used for these studies, they were limited to "bar type" or premises size and failed to consider the past history of alcohol-related harm and opening hours - characteristics that may also predict levels of violence and intoxication. Moreover, past trials have failed to account for the displacement or diffusion effects of premises-level interventions which may undermine evaluations of intervention effectiveness.

This paper reports upon the design of an exploratory trial of a targeted, risk factor-focused intervention, the Licensed Premises Harm Reduction Initiative (LPHRI), which identifies high risk premises using a risk factor prevention approach designed to reduce alcohol intoxication and disorder in licensed premises. Details of the intervention are now described.

## The Licensed Premises Harm Reduction Initiative intervention

• High risk premises are identified through the analysis of routine data (police and ED recorded assaults)

• Premises risk factors for intoxication and disorder are assessed using an audit consisting of two premises walkthroughs (day and night) and one face to face interview with the premises manager. Major categories of risks cover the external environment immediate to the premises, the staff, customer behaviour, the internal physical environment, operational procedures, and security measures.

• Results from the audit inform a bespoke premises action plan, delivered to premises managers in the experimental condition only, that identifies risk factors and suggests solutions. Premises managers will be telephoned one week later to ensure the action plan had been received.

• A second audit, identical to the first, is delivered three months later to assess distance travelled and to provide feedback.

Premises-level interventions have not been trialled in the UK and therefore effect sizes are unknown, prompting the need for an exploratory trial. This study aimed to identify optimum methods for identifying and recruiting premises, the development of a sustainable and rigorous evaluation methodology, the description of matching and randomisation procedures, the identification of appropriate outcome measures, and an understanding of intervention implementation. Particular challenges present themselves in identifying and recruiting high risk premises to such studies; these are outlined and their implications for any definitive RCT of the intervention are discussed.

The study sought to identify methods for intervention targeting, facilitating trial recruitment, developing and maintaining rigorous research designs and identifying and collecting appropriate outcome measures. The qualitative nested process evaluation examined views on intervention theory and acceptability, implementation processes and fidelity, assessed potential contamination between trial arms and identified the structures required for any definitive trial.

## Methods/Design

### Study design

Figure 1 provides a summary of the study, a mixed methods exploratory RCT with nested process evaluation. All aspects of this study were evaluated and approved by the Cardiff University Medical and Dental School Research Ethics Committee (Ref: MDSREC 08/11). Methods were informed by a previous study examining alcohol misuse and violence in the NTE funded by the Alcohol Education Research Council (CA04/01) [13,14].

**Figure 1 F1:**
[figure not shown]
**Study Design**.

### Recruitment

As the characteristics of NTEs and the violence prevention resources available can vary considerably across jurisdictions, the study team implemented the intervention across five towns (reduced to four areas for analytical purposes as two towns, D and E in Table 1, are in close proximity and are typically referred to as an homogenous region). The four areas covered by the study were selected as they featured NTE types representative of those in England and Wales, including cities and small to medium-sized towns.

**Table 1 T1:** Recruited premises by recruitment intensity

Recruitment Strategy	Town A	Town B	Town F	Town D	Town E	Town C
Resident population	325,000	227,000	50,000	47,000	35,600	37,000
**Number of eligible licensed premises**	**89**	**81**	**30**	**11**	**9**	**10**
**Invitation letters sent**	89	81	30	26		
**Expression of interest**	4	2	1	1		
**Recruited**	2	1				

**Premises managers forum**						
**Number of eligible licensed premises**	30	25	10			
**Expression of interest**	2	3				
**Recruited**	1	3				

**Premises visits with police**						
**Number of premises targeted**						6
**Recruited**						6

**Premises visits, no police**						
**Number of premises targeted**	2	7		6	2	2
**Recruited**	2	7		6	2	2

A variety of recruitment strategies that varied in intensity were piloted in phases across the intervention areas. Local police in each area were aware of and supportive of the project. However, they were not involved either in the design or evaluation of the intervention. While it was desirable that police involvement be kept to a minimum in order to facilitate transparency, it was concluded that local police licensing officers represent the most efficient route for accessing and recruiting licensed premises managers. Therefore, licensing officers were involved in the recruitment methodology. Premises were first invited to participate by letter, following which researchers made appeals at premises manager meetings. Once these first two options were exhausted, visits to premises were made by Project staff. All visits involved police officers, either directly through accompanying researchers or indirectly through officers introducing the study to premises staff beforehand. This order was maintained where possible, however due to the timing of some local meetings, the availability of premises staff and Project time constraints, it was not possible to follow this order of events strictly in each area. Irrespective of a premises pathway into the study all premises were visited by a member of the research team before the study commenced in order to describe the project in detail, to allow representatives to ask questions, and to gain verbal consent. Each premises representative was given a detailed description of the trial and what would be required of them.

### Inclusion/exclusion criteria

Premises were eligible for inclusion if (1) a police-recorded violent offence took place in or immediately outside the premises in the twelve months before recruitment, (2) or an attendance at an ED for violent injury was associated with the premises or (3) the premises was identified as being at high risk of disorder by the local police licensing officer. It is likely that police records represent a conservative estimate of the number of serious violent incidents in and around the target premises as it has been demonstrated that the majority of serious violent incidents are not reported to the police [17], but police data are likely to reflect information on incidents where no ED attendance is required, suggesting that a composite dataset is appropriate.

### Matching

The unit of allocation was the individual licensed premises, stratified by risk of harm and area. A risk index was calculated for each licensed premises using the formula Risk = P/(T*C) where P is the number of police recorded incidents in the twelve months preceding project start, T is the number of hours open after 11 pm on Friday and Saturday night and C is the maximum premises capacity. Matching was incorporated into the study to reduce possible imbalances between treatment arms expected with a small sample size, but was not accounted for in subsequent analyses due to the loss of degrees of freedom [18].

### Randomisation

The exploratory trial was a two-armed parallel cluster randomised trial in which premises was the unit of randomisation. Only once the audits and action plans for all thirty-two premises had been completed did randomisation take place. Each premises in a pair was assigned the number one or two in the order they were recruited by Researcher 1. Independently a random number was generated and relayed by telephone to Researcher 1. If an odd number was generated, the premises identity marked one was placed in an envelope and sealed. If an even number was generated, the premises identity marked two was placed in an envelope and sealed. Unselected premises names were placed out of sight. Researcher 1 left the randomisation room and was replaced by Researcher 2. A random number was independently generated and relayed by telephone to Researcher 2. If an odd number was generated, the premises identity in the envelope was allocated to the control group. If an even number was generated, the premises identity marked was allocated to the intervention group. Each premises had a 50% chance of being in either control or intervention group.

### Blinding

The research team members who were responsible for the delivery and evaluation of the intervention were blind to the intervention condition of each premises, as were all data collection staff. Bespoke intervention documents were prepared for all premises by a member of the intervention team although these documents were only delivered to intervention premises. These documents were prepared for delivery by a member of the university administrative staff who played no other part in the study. Since part of the process evaluation required asking different questions of intervention and control premises representatives, the research team members who conducted the process evaluation were necessarily unblinded.

### Measures

The outcome measures used in the study were selected for their appropriateness and objectivity in identifying and accurately associating violence, severe intoxication and environmental disorder with study premises. Identical outcome measures were used at baseline and at the three month follow-up to measure violence, severe intoxication and environmental disorder.

#### Police records

Police records of violence against the person inside or entering or leaving the premises were used as a measure of disorder. An incident was also deemed to be associated with a premises if a participant involved in the incident had been in the premises or attempted to enter the premises immediately prior to the incident.

#### Emergency Department data

Any attendance for treatment of violent injury that was recorded as such in ED records and was associated with a study premises was counted as a violent incident.

#### Environmental observations

Surveyors recorded levels of environmental disorder and contextual risk factors, as well as keeping a continuous record of the characteristics of clients entering and exiting study premises. These records also included details of specific disorder-related incidents, such as ejections from licensed premises, fights and arrests.

#### Patron survey

The survey questions covered respondent gender, age, marital status, employment status, smoking habits, drinking locations and number of people in their group that evening and their intended destination (named premises, home etc.). In addition, the survey incorporated the established Fast Alcohol Screening Test (FAST) [19] - a series of four questions often used to select individuals for brief interventions for alcohol misuse, and three items on respondent's experiences of violent victimisation and violent offending in the preceding twelve months.

#### Breath alcohol concentration

While the police record information on the circumstances of disorder and violence, objective measures of intoxication are not routine and were therefore collected by surveyors. Respondents were breathalysed using a Lion Laboratories SD-400 alcometer and had their BrAC recorded. Surveyors also responded to questions eliciting their subjective measure of drunkenness for respondents who did and did not provide a BrAC. These measures were used to assess potential sampling biases. Alcometers were recalibrated at least one every three months using the manufacturer's equipment and methods.

### Data collection

#### Police data

A data processing agreement between Cardiff University and South Wales Police facilitated data sharing. Data were encrypted and anonymised before transmission to Project staff who interrogated the data for instances of disorder in or around study premises. Incidents were then collated for analysis.

#### ED data

Information collected about patients who have attended an ED as a result of violent injury represents a valuable source of data on violence against the person [20]. Some EDs routinely record detailed information about the patient and the circumstances of the violent incident, including the location of the assault, the number of assailants and injury severity. However, this practice is not universal with some EDs simply recording victim information such as age and time of attendance. At baseline, detailed information about the location of assaults resulting in ED attendance was only available for Town A (see Table 1) across the duration of the baseline period. Data were available for Town B but only for a three-month period. No ED data were available for the remaining areas. A data sharing agreement between Cardiff University and hospitals local to study premises facilitated data sharing. Data for the available time periods were requested from the hospital information services. A Senior Information Analyst retrieved, anonymised and formated these data before transmission to Project staff who interrogated these data for instances of disorder in or around study premises. Incidents were then collated for analysis.

#### Street observations, surveys and breath alcohol concentration data

A surveyor standing four to five metres from the main entrance to a premises carried out environmental observations for the duration of the data collection episode. This involved the continuous observation of pedestrians moving to and from the study premises, a spot survey of environmental conditions every 30 minutes and recording and describing any disorderly or violent incident in the immediate area, such as ejections, fights and arrests. A second pair of surveyors recruited every seventh individual walking past a designated point near to the study premises and asked them to take part in a survey. If the person assented then the surveyor proceeded to ask the survey questions. All survey responses were completed by the surveyors on behalf of the respondents. On completion, respondents were asked to provide a BrAC reading using the alcometer. This was recorded. Once the respondent had left the vicinity, the surveyor rated them on the four descriptors used to identify drunkenness: gait, eyes and speech [14] and overall drunkenness along a 10-point Likert scale. All potential respondents who did not agree to participate were scored on the same subjective descriptors so that potential sampling biases could be assessed.

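### Respondents are rated for drunkenness after an interview and a recorded BrAC, refusers on brief contact with no reading, so the respondent–refuser gap used to check sampling bias is confounded with rating conditions

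*Protocol article*

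**What the plan says.** Surveyors approach every seventh person passing a set point near the premises. The section on street observations, surveys and breath alcohol concentration data then gives the order for those who agree. The survey comes first. Next, "On completion, respondents were asked to provide a BrAC reading using the alcometer. This was recorded". After that, "Once the respondent had left the vicinity, the surveyor rated them on the four descriptors used to identify drunkenness". The descriptors are gait, eyes, speech and overall drunkenness, the last of these on a 10-point Likert scale.

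For those who decline, the same section says: "All potential respondents who did not agree to participate were scored on the same subjective descriptors so that potential sampling biases could be assessed".

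The section on breath alcohol concentration says who took the readings ("objective measures of intoxication are not routine and were therefore collected by surveyors") and who was rated ("Surveyors also responded to questions eliciting their subjective measure of drunkenness for respondents who did and did not provide a BrAC"). It gives the purpose of the ratings: "These measures were used to assess potential sampling biases".

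The only masking described for data collectors is in the Blinding section: they "were blind to the intervention condition of each premises, as were all data collection staff".

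**The concern.** A non-response check asks whether people who refuse differ from people who take part. For that, both groups must be rated in the same way. Here the scale is the same but the conditions are not, and the difference in conditions coincides exactly with the comparison being made. A rating given after a full conversation and a BrAC value can be pulled towards that value. A refuser's rating cannot.

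BrAC is a named outcome and severe intoxication is the intervention's target. It is plausible, though not documented, that drunker patrons refuse more often. The ratings are the only check on refusal that the article describes: FAST scores and violence history exist only for people who took the survey. The article itself warns in its Background that subjective ratings are open to bias. The trial also exists partly to settle data collection methods for a larger study, so a weak check would be carried forward.

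**Working it through.** The plan states no figure to reproduce, because the point concerns the order of measurement. Set side by side, the rating conditions are:

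- **Respondents with a reading:** full interview; BrAC taken and recorded; rated after they leave.
- **Respondents without a reading** (if this means people interviewed but not breath-tested): full interview; no BrAC.
- **Refusers:** brief approach only; no interview; no BrAC.

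The first and third groups differ in two ways besides willingness to take part: length of contact and availability of a reading.

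A simple model shows what this can do. All its inputs are assumptions. Let:

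- T be true drunkenness on the 10-point scale;
- b be the amount by which unaided raters under-score;
- e be random rating error;
- w (0 to 1) be the weight a rater gives to a known reading;
- d be the true amount by which refusers are drunker than respondents.

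Unaided rating: u = T − b + e.
Rating with the reading known: a = (1 − w)u + wT = T − (1 − w)(b − e).
Expected refuser-minus-respondent gap: (d − b) + (1 − w)b = d − wb.

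The distortion is therefore wb.

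*No true selection (d = 0).* Respondents falsely appear drunker than refusers by wb:

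| b | w = 0 | w = 0.25 | w = 0.5 | w = 1 |
|---|---|---|---|---|
| 0 | 0 | 0 | 0 | 0 |
| 0.5 | 0 | 0.125 | 0.25 | 0.5 |
| 1.0 | 0 | 0.25 | 0.5 | 1.0 |

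A simulation of 400,000 people per group agreed with these values to within about 0.02 points.

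*True gap of 1 point (d = 1).* With wb from 0.5 to 1.0, the observed gap is 1 − 0.5 = 0.5 down to 1 − 1 = 0. If unaided raters over-score, so that wb runs from −0.5 to −1.0, it is 1.5 to 2.

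*Spread.* With an assumed true SD of 2 and rating-error SD of 1.5, the unaided SD is √(4 + 2.25) = 2.5. With the reading known it is √(4 + (1 − w)² × 2.25), which gives 2.3, 2.1 and 2.0 for w = 0.25, 0.5 and 1. The two sets of ratings then differ in precision even when b = 0.

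Longer contact may add a further shift, c, to respondents' ratings, making the observed gap d − wb − c. Refusers receive neither w nor c, so refuser ratings compared between arms or periods do not contain these terms.

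**The case against.** The strongest reply is that the article never says the rater saw the reading. The recording is described in the passive, surveyors worked in pairs, and a condensed article may leave such field detail to the full protocol. This stands as a limit on certainty. But surveyors collected the BrAC, the text speaks of a single surveyor doing the rating, and no separation is described. The unequal contact time also remains whoever read the alcometer.

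A second reply is that interviewed people without a reading could separate the effect of the reading from that of the interview. They help only in part: they chose not to be tested, so they may differ in drunkenness too.

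A third is that this is a descriptive check in an exploratory trial that did not expect a significant effect. That is fair, and it limits the weight of the point.

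A reader might go further than the documents allow in three ways:

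- **That the BrAC outcome or the between-arm comparison is biased.** BrAC is an objective reading taken before the rating. Data collectors were blind to arm, and one procedure is described for all premises, so differential distortion by arm is not shown.
- **That the ratings fail as a basis for imputing or weighting for refusers.** The article plans neither; it uses the ratings only to assess sampling bias.
- **That half or all of a selection effect is being hidden.** Those figures follow from assumed inputs. The distortion is zero if unaided raters are unbiased, or ignore the reading, and contact time has no effect.

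**Conclusion.** The point holds, within a narrow scope. In the stated order, the absolute respondent-versus-refuser difference in rated drunkenness mixes selection with rating conditions. Neither a gap nor the absence of one can be read with confidence as evidence about sampling bias. Size and direction are unknown; the illustration spans 0 to 1 point either way on a 10-point scale.

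The conclusion rests on the plain reading that the surveyor who rates also knows the recorded BrAC. If the rater did not know it, only the contact-time difference remains. BrAC readings, refusal rates, and refuser ratings compared between arms or periods are not directly affected. This is a worthwhile, inexpensive improvement to a secondary check, not a threat to the trial's main comparison.

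**What to change.** Change the order in the section on street observations, surveys and breath alcohol concentration data. For every seventh person, score gait, eyes, speech and overall drunkenness at first approach, before the survey and the alcometer, whether or not the person takes part. Use that score for the respondent–refuser comparison and report it by arm and period. This removes both knowledge of the reading and unequal contact. Moving the rating only to just before the breath test would remove the first but not the second.

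The descriptors and staff stay the same; the change is mainly to the order of the form. The costs are that eyes and speech are judged on briefer contact, so the score is noisier, and that it is made while the person is still present, which needs some discretion.

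The article describes baseline surveys as already entered. If those ratings were made in the stated order, keep the post-reading rating at follow-up alongside the new one so that the periods remain comparable, and report the baseline comparison with this limitation. Use the new order in any definitive trial. An imputation analysis of BrAC using the new score is optional and is not needed to correct this point.
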